#### 2.9.2. Pulmonary Artery Catheter (Swan-Ganz—Catheter)

To quantify the extend and severity of cardiac shock and improvement under mechanical cardiac support (MCS), hemodynamic measurements will be obtained by pulmonary artery catheter and include pulmonary capillary wedge pressure (PCWP), mean right atrial pressure (RA) central venous oxygen saturation (cvSo2), and mixed venous oxygen saturation (mvSO2).

The following parameters will be calculated: cardiac index (CI), stroke volume (SV), systemic vascular resistance (SVR), pulmonary vascular resistance (PVR), and cardiac output (CO). At the trial site, the pulmonary artery catheter Corodyn TD^®^ (B. Braun^®^, Melsungen, Germany) will be used. This 4-lumen catheter is inserted with the cardiac catheterization lab either through the femoral or jugular vein before Impella^®^ placement and has a caliber of 7 Fr and a length of 110 cm.

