The largest randomized trial of MCS in patients with CS, IABP Shock II, did not show any advantage of mechanical cardiac support using intra-aortic balloon counter-pulsation (decrease in afterload without active unloading of the failing left ventricle) compared to a conservative medical strategy of shock treatment [17]. Implantation of mechanical assist devices such as veno-arterial extracorporeal membrane oxygenation (VA-ECMO) is currently the only therapeutic option for stabilizing refractory cardiac shock patients [17,18,19]. However, due to the invasiveness of the procedure, there is a risk of bleeding, stroke, infections, sepsis, and limb ischemia [1]. In addition, VA-ECMO increases left ventricular end-diastolic pressure as well as afterload that again leads to increased wall stress and myocardial oxygen demand [20].

In contrast, Impella^®^ is a mechanical unloading device through placement in the left ventricle with continuous blood flow from the left ventricular cavity to the ascending aorta. It has been approved for the stabilization of patients with cardiogenic shock. It facilitates unloading of the left ventricle to support contractility independently from heart function and rhythm via adjustable flow rates. A dissociation of left ventricular peak pressure from aortic pressure can be achieved with higher mean arterial pressure. The pressure-volume loop of the left ventricle is shifted leftwards resulting in a lower left ventricular end diastolic pressure, a diminished pressure-volume area, lower left atrial and pulmonary wedge pressure, decreased myocardial oxygen consumption, and a reduction in the left ventricular wall tension [4]. Nevertheless, no study has systematically analyzed markers of myocardial unloading using Impella^®^ in patients with cardiogenic shock.

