### 2.3. Study Population

JenaMACS includes critically ill patients with cardiogenic shock and indication for an extracorporeal, mechanical, circulatory assist device determined by corresponding PAC (pulmonary artery catheter) hemodynamics (mean arterial pressure (MAP), pulmonary wedge pressure (PCPW), pulmonary artery pressure (PAP), pulmonary vascular resistance (PVR), systemic vascular resistance (SVR), mixed venous oxygen saturation (mvO2Sat), SV (stroke volume)). Inclusion and exclusion criteria are listed in Table 1.

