### 2.6. Objectives

#### 2.6.1. Primary Objective

The primary objective of the JenaMACS register is to investigate the potential benefit of the Impella CP^®^ on hemodynamics and left ventricular unloading in patients with cardiogenic shock after 24 h by using a ramp test protocol (Table 2 and Figure 1). The ramp test is performed as follows: During a step by step reduction of the Impella^®^ flow support (ramp test), hemodynamic (PCWP, SV) and echocardiographic parameters (left ventricular ejection fraction (LVEF), left ventricular end-diastolic diameter (LVEDD), and grading of mitral valve regurgitation) are recorded at each level from highest (P8) to lowest (P2). Measurements take place 10 min after adjusting the console to each flow level. In theory, mechanical assistance for unloading of the left ventricle might lead to a faster decrease in LVEDD, PCWP and mitral regurgitation and faster increase in LVEF and SV that could be translated into improved left ventricular recovery

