### 2.9. Technology to Be Used

#### 2.9.1. Impella^®^

The Impella CP^®^ (Abiomed, Danvers, MA, USA) used for JenaMACS is an axial, non-pulsatile, continuous 14 Fr magnetic levitation propeller pump delivering a maximum flow of 3–4 L per minute. Inserted percutaneously via Seldinger technique, the Impella^®^ is then advanced retrograde from the common femoral artery, through the aorta and across the aortic valve into the LV. An ultrasound-assisted puncture of the femoral artery can be performed to minimize access site complications. The device is using an impeller to eject blood from the left ventricle into the ascending aorta via a tube. The pump is not dependent on pulsatile flow or EKG. The impeller speed defines the flow rate of the device and therefore the blood volume to be ejected. Maximal flow rate for ImpellaCP^®^ is 3.5 L/min. Flow rate adjustments can be set manually from an external console and are the basis of the ramp test 24 h after Impella CP^®^ implantation (Table 2 and Figure 2). Flow rate also depends on the preloading of the left ventricle.

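### Catheter-derived stroke volume contains the pump flow that the ramp test varies, so it cannot by itself support a reading of left ventricular recovery

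*Protocol article*

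**What the plan says.** - **Role of SV.** Section 2.6.1 lists "hemodynamic (PCWP, SV) and echocardiographic parameters" as recorded at each support level from P8 down to P2. It then offers a cautiously worded rationale, that unloading might bring a "faster decrease in LVEDD, PCWP and mitral regurgitation and faster increase in LVEF and SV that could be translated into improved left ventricular recovery".
- **Source of SV.** Section 2.9.2 (pulmonary artery catheter) states: "The following parameters will be calculated: cardiac index (CI), stroke volume (SV), systemic vascular resistance (SVR), pulmonary vascular resistance (PVR), and cardiac output (CO". Section 2.3 also places SV among the catheter values: "mixed venous oxygen saturation (mvO2Sat), SV (stroke volume". The echocardiography section (2.9.3) names no SV. No formula is given, and nothing says whether SV means total or native.
- **What the pump does.** Section 2.9.1: "The device is using an impeller to eject blood from the left ventricle into the ascending aorta via a tube". The maximum flow "is 3.5 L/min. Flow rate adjustments can be set manually from an external console and are the basis of the ramp test". The same section also gives 3–4 L/min.
- **Primary parameter list.** Section 2.7 refers to Table 2 for the parameters of the primary endpoint. Table 2 has columns for Flow, HR, CI, PCWP, MR, LVEDD and LVEF, among others, but none for SV.

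**The concern.** The stated source of SV and its stated reading do not fit together while the pump is running. The pump works in parallel with ejection through the aortic valve, so output measured on the right side of the heart is the sum of the two flows. Dividing that sum by heart rate spreads continuous pump flow over the heartbeats and gives total flow per beat, not the stroke volume of the ventricle.

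The ramp test deliberately changes pump flow. An SV derived this way therefore contains the manipulated variable. A higher value at P8 than at P2 may be wholly or partly delivered pump flow, and it could appear even when the ventricle itself ejects less at P8. At stake is what may be concluded from one of the two hemodynamic parameters named in the primary objective, in a single-arm study of 20 patients.

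**Working it through.** The article states no figure on this point to reproduce. The check is a flow balance.

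**Inputs**
- Stated: maximum pump flow 3.5 L/min, also given as 3–4 L/min (Section 2.9.1); ramp from P8 to P2 (Section 2.6.1, Table 2).
- Not stated, assumed here: heart rate 90/min (range 80–110); total CO at P8 4.5 L/min; pump flow 3.5 L/min at P8 and 1.5 L/min at P2 (range 1.0–2.0 at P2).
- Inferred: calculated SV = CO/HR. At steady state, right-sided output equals total systemic flow.

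**Step 1. Formulas**
- CO = native flow + pump flow
- Calculated SV = CO/HR
- Native SV = (CO − pump flow)/HR

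**Step 2. Pump share of calculated SV**
At 3.5 L/min: 3500/80 = 43.8 mL, 3500/90 = 38.9 mL, 3500/110 = 31.8 mL. Over 3–4 L/min and the same heart rates, the range is 3000/110 = 27.3 to 4000/80 = 50.0 mL.

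**Step 3. Direction of change from P8 to P2**
Let D be the fall in total CO and P the fall in pump flow. At constant heart rate:
- change in calculated SV = −D/HR
- change in native SV = (P − D)/HR

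The signs are opposite exactly when 0 < D < P. If D = 0, calculated SV does not move. If D > P, both fall. If CO rises, both rise.

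**Step 4. Illustration** (HR 90, CO 4.5 at P8, P = 3.5 − 1.5 = 2.0 L/min; at P8, calculated SV = 4500/90 = 50.0 mL and native SV = 1000/90 = 11.1 mL)

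| Fall in CO (L/min) | Calculated SV at P2 (change), mL | Native SV at P2 (change), mL |
|---|---|---|
| 0 | 50.0 (0) | 33.3 (+22.2) |
| 0.5 | 44.4 (−5.6) | 27.8 (+16.7) |
| 1.0 | 38.9 (−11.1) | 22.2 (+11.1) |
| 1.5 | 33.3 (−16.7) | 16.7 (+5.6) |
| 2.0 | 27.8 (−22.2) | 11.1 (0) |
| 2.5 | 22.2 (−27.8) | 5.6 (−5.6) |

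With P2 flow set to 1.0, 1.5 or 2.0 L/min and CO falling by 25–75% of the pump-flow reduction, calculated SV changes by −4.2 to −20.8 mL and native SV by +4.2 to +20.8 mL.

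**Step 5. Sensitivity**
- Heart rate rising from 90 to 100 with CO 4.5 to 4.0: calculated SV 50.0 to 40.0 mL, native SV 11.1 to 25.0 mL. The signs are still opposite.
- A wider grid of assumed values, restricted to falling CO (HR 80–110, P8 flow 3.0–4.0, P2 flow 1.0–2.0, CO 4.0–5.5 at P8 and 3.0–5.0 at P2): opposite signs in 279 of 378 combinations, not in the other 99. This share describes the grid. It is not a probability for patients.

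**Step 6. Which other parameters are affected**
CI is CO divided by body surface area, so the CI column of Table 2 includes pump flow too. PCWP, LVEDD and MR are not derived from CO and do not share this problem.

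**The case against.** The case on the other side has real force.

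- **The formula is inferred.** CO/HR is never written, and a condensed article may leave the derivation to the full protocol. That stands as a limit. However, the article does state the source of SV and a reading for it, and the two conflict under the plain derivation. The point is more than a missing formula.
- **SV is absent from Table 2.** Its place in the primary endpoint is therefore uncertain. This stands and has to be reconciled, but SV is still named in the primary objective, and CI, which is in Table 2, carries the same pump contribution.
- **The recovery sentence is hedged.** It is a theoretical remark about speed of change, not a rule for comparing P8 with P2. A reader might infer that a higher SV at P8 will be reported as better ventricular function. The article nowhere says so.
- **Total flow is a legitimate result in shock.** True: as a systemic-flow outcome, CO/HR is sound. Unloading is also judged by PCWP, LVEDD and MR, so the stronger inference that the trial's whole question would be answered by an artefact is not supported.
- **Opposite movement is not guaranteed.** A reader might infer that the two quantities always diverge. That result appears only if the fall in CO is assumed smaller than the fall in pump flow; Step 3 gives the exact condition.
- **Native SV is no clean substitute.** It carries pump flow with a negative sign. In the first row of the table, total CO is unchanged, yet native SV differs by 22.2 mL purely because pump flow differs. Used alone, it could make effective unloading look like worse function.
- **Nothing is lost.** Flow, CI and HR are recorded at each level, so the split can be made at analysis. That makes the repair cheap; it does not make the unsplit quantity a ventricular measure.

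**Conclusion.** The concern holds in a limited form. SV as most plausibly derived is total flow per beat, contains the flow that the ramp test manipulates, and cannot by itself support the recovery reading in Section 2.6.1. The pump's contribution is large on illustrative values: 27.3 to 50.0 mL per beat over the stated 3–4 L/min at assumed heart rates of 80–110/min.

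Reversal against native SV is an algebraic possibility under a clear condition, not an established outcome. The conclusion rests on SV being CO/HR and on right-sided output equalling native plus pump flow. It does not depend on the assumed CO, heart rate or P2 flow, which set only the sizes. It does not invalidate the primary endpoint as a whole.

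**What to change.** 1. In Sections 2.6.1 and 2.9.2, state the SV formula, label CO/HR (and CI) as total systemic flow, and do not read it as left ventricular stroke volume.
2. Beside it, at P8, P6, P4 and P2, report native SV = (CI × body surface area − Impella flow)/HR, using the Flow, CI and HR columns already in Table 2. Note that console flow is an estimate, and that native SV is load-dependent and falls mechanically as pump flow rises.
3. Interpret neither SV measure alone as ventricular recovery; read both together with PCWP, LVEDD, LVEF and MR.
4. Reconcile Section 2.6.1, which names SV for the ramp test, with Table 2, which omits it.

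The cost is one derived variable and some rewording. Body surface area is the only input to the formula outside Table 2, and it is already needed to calculate CI. The ramp test and patient management are untouched. The downside is that native SV brings in the measurement error of the console flow.

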#### 2.9.3. Transthoracic Echocardiography

Transthoracic echocardiography (TTE) is performed using the ultrasound system Vivid S70^®^ (GE^®^, Boston, MA, USA) and the recordings are processed via dedicated software (Image-Arena ™ Version 4.6; TomTec Imaging Systems, Unterschleissheim, Germany). Echocardiographic evaluation is carried out in a standardized comprehensive fashion and encompasses acquisition of features of left/right ventricular and valvular function (Table 2).

### 2.10. Safety, Possible Complications and/or Risks

Study participation is not associated with any additional risks for patient’s safety. The Impella CP^®^ is a CE-approved medical device and part of routine, clinical use for cardiogenic shock and other indications. The use of a Swan-Ganz Catheter is standard practice in cardiogenic shock patients. For safety assessments, documentation of relevant events regarding Impella CP^®^ treatment include the aspects listed in Table 5.

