### 2.7. Endpoints

The primary endpoint of the JenaMACS register study is the change in hemodynamic and echocardiographic parameters after 24 h during the ramp test at different Impella^®^ support levels. Parameters to be measured are listed in Table 2 and a scheme is provided in Figure 2. Secondary endpoints are listed in Table 4.

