#### 2.12.5. Supportive Therapy in the Intensive Care Unit

Further intensive medical therapy is carried out according to generally recognized guidelines. Systemic anticoagulation with unfractionated heparin will be used for the duration of left ventricular support (target activated clotting time around 180 s).

Drug therapy with catecholamines (noradrenaline, dobutamine, possibly suprarenin, vasopressin) according to current recommendations is possible. The use of calcium sensitizers (e.g., levosimendan) or other hemodynamically relevant drugs (e.g., PDE inhibitors) are also possible according to an individual intensive care medicine assessment [14]. The aim, independent of the study, is to achieve a mean arterial blood pressure of at least 65 mmHg. All patients receive an invasive hemodynamic measurement using a standard pulmonary artery catheter. The daily doses of catecholamines and other hemodynamic drugs are documented. Furthermore, the daily fluid balance/management up to the explanation are recorded. If the use of a renal replacement therapy is necessary, the duration and type of the procedure are documented. In addition, the duration of any mechanical ventilation, the time of extubation and any reintubation that may be necessary are documented. Left ventricular ejection fraction is determined again within 24 h and after 7 days.

As part of the recording of the intensive medical treatment, the SAPS (Simplified acute physiology score) II score is recorded serially every day in the intensive care unit. To determine inflammatory parameters, as well as liver and kidney functions, a full blood work-up is recorded daily including C-reactive protein (CRP) and procalcitonin (PCT). All other laboratory parameters are determined at least once a day according to the documentation sheets in the routine laboratory program. Ethylenediaminetetraacetic acid (EDTA), blood, serum and plasma are stored at all times (before, after implantation, day 1–3 and 7) for later molecular biological analysis.

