#### 2.12.7. Weaning and Explantation of the Impella CP^®^ Device

The duration of therapy is determined by the need for supportive therapy with catecholamines. In previous studies, the mean duration of mechanical circulatory support was 3–4 days [21]. The main criterion for starting weaning from mechanical circulatory support is sustained hemodynamic stability (systolic RR > 90 mmHg for >60 min) without therapy with catecholamines and without signs of peripheral end-organ hypoperfusion. Impella^®^ flow is reduced in steps every 3 h; after 3 h at level 2, another echocardiography, hemodynamic measurement and blood sampling followed by explanation of the Impella^®^ take place. Standardized femoral artery access site closure takes place after explantation via a suture mediated percutaneous system as a first option (Perclose ProGlide^®^, Abbott laboratories, Abbott Park, Chicago, IL, USA)

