**Figure 2 jcm-11-04623-f002:**
[figure not shown]
Study set up for measuring the primary outcome after 24 h of Impella^®^ support post-implantation via PAC and TTE(Graphic generated using BioRender©).

**Table 1 jcm-11-04623-t001:** Inclusion and exclusion criteria of the JenaMACS study.

Inclusion	Exclusion
- Systolic blood pressure < 90 mmHg, >30 min of inotropic agents and/or vasopressors to keep the blood pressure > 90 mmHg systolic - Signs of left ventricular failure with pulmonary congestion. - Signs of end-organ hypoperfusion with at least one of the following criteria: - Somnolence. - Cold, pale skin or extremities. - Oliguria (≤30 mL/h). - Serum lactate > 2.0 mmol/L. - Age ≥ 18 years ≤90 years. - Signed informed consent	- Contraindications to Impella CP^®^ implantation. - Shock duration > 12 h before evaluation. - Severe PVD making Impella implantation impossible. - Aortic valve insufficiency/stenosis at least II°. - Age > 90 years. - CNS disease with fixed, dilated pupils (not drug-induced). - Severe concomitant disease with limited life expectancy < 6 months. - Participation in another study. - CPR > 30 min. - Shock due to other reasons.

CNS = Central nervous system, CPR = Cardiopulmonary resuscitation, PVD = Peripheral vessel disease.

**Table 2 jcm-11-04623-t002:** Ramp Test protocol: A ramp test will be performed 24 h after Impella CP^®^ implantation according to the following protocol.

Speed	Flow	Mean BP	HR	PCWP	Mean PA	PAO2	Lactate	CI	MR	LVEDD	LVESD	LVEF	RVEDD
	[L/min]	[mmHg]	[L/min]	[mmHg]	[mmHg]	[%]	[mmol/L]		[Degree]	[mm]	[mm]	[%]	[mm]
**P8**													
**P6**													
**P4**													
**P2**													

BP = Blood pressure; HR = heart rate; PCWP = Pulmonary, capillary wedge pressure; PA = Pulmonary artery; CI = Cardiac index; LVEDD = Left ventricular end-diastolic diameter, LVESD = Left ventricular end-systolic diameter; LVEF = Left ventricular ejection fraction; RVEDD= Right ventricular end-diastolic diameter; T = Impella flow level, MR = Mitral regurgitation.

**Table 3 jcm-11-04623-t003:** Frequency and scope of the JenaMACS study visits.

					Time Point					
Protocol Item	Pre PCI	Post-PCI	Day 1	Day 2	Day 3-X *	Stabilization ^+^	Day 7/E	30 Rays	6 M.	12 M.
Inclusion/exclusion criteria	X									
Informed consent	X									
12-lead surface ECG	X	X	X	X	X	X	X	X		
Laboratory evaluation ^∆^	X		X	X	X	X	X			
Medical history, Comorbidities ^∆^	X									
Physical examination ^∆^	X	X	X	X	X	X	X	X	X	X

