BGA including lactate	X	X	X	X	X	X				
Creatinine clearance **	X		X	X	X					
Blood Samples (Measurement of biomarkers)	X	X	X	X	X	X	X	X	X	X
PAC—Hemodynamics	X	X	X	X	X	X				
Measurement of parameters of hemodynamics ^∆^	X	X	X	X	X	X				
TTE	X	X	X	X	X	X	X	X		
Dose of isotopes and vasopressors	X	X	X	X	X	X	X	X		
Impella CP^®^ data	X	X	X	X	X	X				
SAPS-II Score		X	X	X	X	X				
CCS category								X	X	X
NYHA category								X	X	X
Quality of Life (EQ-5D)							X	X	X	X
Measurement of the neurological outcome (GCS) ^∆^	X	X	X	X	X	X	X	X	X	X

^∆^ Data documentation from clinical routine (if available), * every day until hemodynamic stabilization; ** Clearance calculated according to Cockcroft-Gault formula; ^+^ after Impella explantation; SAPS = Simplified Acute Physiology Score; ECG = Electrocardiography; TTE = Transthoracic echocardiogram; PAC = Pulmonary artery catheterization; NYHA = New York Heart Association; CCS = Canadian Cardiovascular Society; GCS = Glasgow coma scale; PCI = Percutaneous, coronary intervention; BGA = Blood gas analyses. EQ—5D = EuroQol questionnaire.

**Table 4 jcm-11-04623-t004:** Secondary endpoints of the JenaMACS study.

Secondary Endpoints
- Change of hemodynamic and echocardiographic parameters after 10 min, 30 min and every 8 h of Impella support - Need, type, dose and duration of inotropic/vasopressor treatment. - Time until hemodynamic stabilization (lactate < 2 mmol/L; mean arterial pressure > 65 mmHg) after implantation. - Change in inflammatory parameters over time. - Mean and area under the curve of serum-lactate measured every 8 h for 48 h after implantation. - Mortality defined as mortality rate in the hospital or anywhere after discharge, within 12 months after implantation. - Changes in kidney function after implantation. - Need and duration of renal replacement therapy (CVVHD) and mechanical ventilation after implantation. - Length of stay at ICU after implantation. - Need for an active assist device or heart transplantation after implantation. - SAPS II Score at baseline and every 24 h during Impella CP^®^ support. - EQ-5D-questionnaire including EQ VAS after implantation. - Neurological outcome (GCS) after implantation. - Safety aspects such as major bleeding according to GUSTO/BARC definition, critical limb ischemia, sepsis, hemorrhagic or ischemic stroke

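### Section 2.10 says participation adds no risk without mentioning the study-scheduled ramp test, and Table 2 records no vasoactive dose at the ramp levels

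*Protocol article*

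**What the plan says.** Section 2.10 states without qualification: "Study participation is not associated with any additional risks". It gives two reasons, the approval and routine use of the device and the standard use of the Swan-Ganz catheter, and then refers to Table 5 for the safety events to be documented.

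Section 2.7 makes the primary endpoint the change in hemodynamic and echocardiographic parameters across support levels in the ramp test at 24 h, and adds: "Parameters to be measured are listed in Table 2 and a scheme is provided in Figure 2". The Table 2 caption fixes the timing: "A ramp test will be performed 24 h after" implantation. Section 2.6.1 describes a stepwise reduction from P8 to P2 and says: "Measurements take place 10 min after adjusting the console to each flow level".

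On drugs, section 2.12.5 permits catecholamines and other hemodynamically active agents and sets a pressure target: "The aim, independent of the study, is to achieve a mean arterial blood pressure of at least 65 mmHg". On records it says: "The daily doses of catecholamines and other hemodynamic drugs are documented". Table 3 lists "Dose of isotopes and vasopressors" (evidently inotropes) by visit, including Day 1. Table 4 has need, type, dose and duration of this treatment among the secondary endpoints.

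**The concern.** There are two linked problems, both arising from the ramp test.

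The first is disclosure. The ramp temporarily lowers circulatory support in patients with cardiogenic shock, at a time set by the study. A statement that participation adds no risk has to cover that procedure, and the reasons given do not. This matters more because section 2.5 provides for sedated or impaired patients to be enrolled on their presumed will, so the risk description is relied on by others.

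The second is interpretation. The abstract acknowledges that there is no comparison group, so the within-patient change across support levels carries the primary evidence. If vasoactive drugs are adjusted while support falls, part of the change in pressure, wedge pressure or cardiac index may be a drug effect. If dose is not recorded at each level, no later analysis can separate the two.

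**Working it through.** **Is the ramp covered by the no-risk statement?**

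- Grounds in 2.10: device and catheter. The ramp is not mentioned.
- Status of the ramp: required by the primary endpoint (2.6.1, 2.7, Table 2). No section describes it as part of usual care.
- Flow reduction described as care: weaning in 2.12.7. It starts once the patient is stable, off catecholamines and free of signs of hypoperfusion, and "flow is reduced in steps every 3 h". The ramp as described states no such precondition.
- Timing: 2.12.7 cites a mean support duration of 3–4 days, so a ramp at 24 h will usually come before weaning.
- Minimum time below P8: levels P6, P4 and P2, each held at least 10 min before its reading, give 3 × 10 = 30 min, of which at least 10 min is at P2. This is time below P8. A patient already running at a lower setting at 24 h spends less time below the clinical setting.
- Table 5 has 11 items, and none names hypotension or hemodynamic worsening during the ramp.

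**Is dose recorded per level?**

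- Table 2 columns after Speed: Flow, Mean BP, HR, PCWP, Mean PA, PAO2, Lactate, CI, MR, LVEDD, LVESD, LVEF, RVEDD = 13. Over four levels, 13 × 4 = 52 entries per ramp, none of them a dose.
- Other dose records: daily (2.12.5), by visit (Table 3), and as a secondary endpoint (Table 4). None is stated to assign a dose to a ramp level. The four levels together take about 4 × 10 = 40 min.
- Permission to titrate: the pressure aim of at least 65 mmHg in 2.12.5 applies independently of the study, and the article does not say that doses are held constant during the ramp.

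**Cost of recording dose**

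- One dose entry per level plus one reason if the ramp is incomplete: 4 + 1 = 5 per ramp; 5 / 52 = 9.6% more; 5 × 20 patients = 100 entries.
- If the four drugs named in 2.12.5 (noradrenaline, dobutamine, suprarenin, vasopressin) are each entered separately: 4 × 4 + 1 = 17 per ramp; 17 × 20 = 340.

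**The case against.** The strongest reply is that the dose point argues from silence. A journal article condenses the protocol, and the case report form may already have a dose field per level or an instruction to keep infusions constant. Table 2 is visibly not the whole ramp record, since 2.6.1 says stroke volume is recorded at each level and Table 2 has no such column. This stands as a limit: if the form captures dose per level, the text only needs to say so. It does not remove the point, because 2.7 itself refers to Table 2 for what is measured, and a plan followed as printed would not collect the dose. The Table 4 endpoint and the Day 1 entry show that doses are recorded, but not that they are tied to a ramp level.

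A second reply is that deterioration during the ramp would be seen. That is right. Table 2 records mean pressure, heart rate, wedge pressure, lactate and cardiac index at every level, 2.11.2 provides for tabulating all observed safety events, and 2.13.1 provides an independent committee for adverse events. A reader might infer from Table 5 that ramp-related harm would go unrecorded; the document does not support that. The defect is in the risk statement.

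A third reply is that a short ramp cannot be judged against weaning. A reader might take the ratio of a 3 h weaning step to a 10 min ramp interval (180 / 10 = 18) as a measure of danger. It is not: weaning ends in removal of the device, and its time at level 2 is longer than the ramp's minimum. The comparison shows only that the ramp is not the flow reduction that the article describes as care. Likewise, dividing a 24 h day by the 40 min ramp (1,440 / 40 = 36) says nothing about bias, because the article does not say that the daily record is one averaged figure.

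**Conclusion.** The point holds in two parts. The no-added-risk sentence in 2.10 is unsupported as written, because its grounds leave out the study procedure on which the primary endpoint depends. As Table 2 is printed, a vasoactive dose change during the ramp could not be separated from the effect of support level, and the other dose records are not stated to resolve it.

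Neither the added risk nor any bias can be sized from the document. Upward titration at low support would plausibly blunt a fall in pressure rather than create an apparent device benefit, and the net effect on the other parameters cannot be derived. A reader might assume that P8 against P2 is the primary contrast; 2.7 speaks only of change at different support levels, so the concern applies to any comparison across levels. Nor does the document show that the ramp is unsafe or that doses are in fact changed.

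The conclusion assumes that the ramp is not already local routine care and that no unseen form captures dose per level. If the first is false, 2.10 should say so. If the second is false, a sentence in the text is enough. Both corrections should be made, since they are cheap and dose data not collected at the bedside may not be recoverable.

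**What to change.** 1. Amend 2.10, and the consent text if it repeats the sentence, to name the ramp test as a study procedure with its own risk.
2. Add inotrope and vasopressor dose at each of the four levels to Table 2, with one entry for the reason if the ramp is not completed.
3. State that doses are kept constant during the ramp unless safety requires a change.
4. Report the number of ramps with a dose change and the number of incomplete ramps, with reasons. Any split of results by dose change should be descriptive only: titration is itself a response to the ramp, so the groups are selected, and they will be small out of 20 patients.

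The cost is one sentence in 2.10, one on constant dosing, and 5 to 17 extra entries per ramp. The downside is slightly more bedside documentation during the ramp.
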